### **6.8. Outcomes**

The outcomes are measured at patient level. Patient's outcomes data will be collected at baseline and at study follow-up points (3 and 6 months). Follow-up data can be collected within 1 month after or before these exact time-point. At baseline, data collection is performed through a face-to-face interview conducted by the pharmacist (before the intervention take place in the intervention arm), by electronic extraction from the pharmacies dispense software and by telephone interview led by the research team after the patient recruitment. Follow-up study data collection is conducted by the research team through patients' telephone interview and electronic extractions from the pharmacies dispense software. Intervention related data will be collected alongside the study.

For process outcomes and economic evaluation analysis, data will be collected from the intervention log form (**Annex 10**), from the case report form "Passaporte do utente" (**Annex 9**) developed for the information exchange between pharmacists and GP, and from the CRA monitoring form (**Annex12**). These materials will be collected for study purposes in the end of the intervention period.

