## DATA COLLECTION, MANAGEMENT, AND ANALYSIS

### 6.12. Data collection, Variables and Definitions

Data will be collected through:

- Structured paper-questionnaire applied to patients by face-to-face interview;
- Structured questionnaires applied to patients by telephone interview;
- Data extractions of medicines consumption from the pharmacy dispensing software and;
- Paper forms filled by the pharmacists and general practitioners during the intervention course.
- Paper form filled by the CRA during the intervention course.

Patient outcomes data will be collected at all study-follow-up points.

Follow-up data for T1 and T2 could be collected within 1 month after or before these exact time-points.

The personal data of the participants (name, telephone number, NHS and NIF) will be collected to enable the patient identification by the health professional and to assure that the research team have timely and appropriate access to essential data to answer the primary objective.

Table 5 summarises the list of variables, time points and data sources that will be collected for this study.

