| Number of Adverse drug events                                                | 
 
• number
 
                                                                | Telephone interview                                | T0, T2 |
| Adverse drug events. Needed support from health professionals?               | 
 
• Yes
 
• No
 
                                                     | Telephone interview                                | T0, T2 |
| Healthcare resource utilization (within the last 6 months -T0 and T2) |                                                                                                                           |                                                    |        |
| Number GP's appointments all                                                 | 
 
• n GP appointments
 
                                                     | Telephone interview                                | T0, T2 |
| Number of Specialty practitioners' appointments                              | 
 
• n medical speciality health care appointments (ex. internal medicine)
 
 | Telephone interview                                | T0, T2 |
| Diagnostic tests or medical exams (gastric system related)                   | 
 
• Yes
 
• No
 
                                                     | Telephone interview                                | T0, T2 |
| Type of Diagnostic tests or medical exams (gastric system related)           | 
 
• To be defined
 
                                                         | Telephone interview                                | T0, T2 |
| Number Diagnostic tests or medical exams (gastric system related)            | 
 
• n diagnostic tests or exams
 
                                           | Telephone interview                                | T0, T2 |
| Diagnostic tests or medical exams with anesthesia                            | 
 
• n
 
                                                                     | Telephone interview                                | T0, T2 |

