## **6.17. Economic evaluation**

### **6.17.1. Overview**

Economic evaluation will be conducted alongside the non-randomized controlled trial, meaning the collection of costs and outcome data alongside the trial.

The economic evaluation will adopt an NHS perspective as base-case, including all health care resource use data and medicines costs, but also a broader perspective in a scenario analysis, including out-of-pocket expenses.

Data will be presented by costs parcel to allow alternative perspectives to be considered separately. The time horizon in the base-case analysis will be of 6 months.

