### **6.17.2. Measurement and valuation of resources**

Health care resource use data will be based on patient-reported data. Data will be collected for the following period: baseline and 6-month follow-up. At baseline, information will cover the previous 6 months; at 6-month follow-up the service use since the previous time-point was recorded (baseline).

Resource-use information will be collected using questionnaires developed by the research team. The following resources, identified on literature (84,101) will be collected: regular medications used, number of doctor's appointments by type and setting (GP and specialist, public and private); number of emergency care episodes, number and major motive of hospitalizations, length of stay (LOS), number and type of diagnostic and therapeutic tests related with gastrointestinal symptoms.

For each item of service use reported in the resource use questionnaires, a unit cost will be applied and the total costs for each individual will be calculated. All unit costs will be for the most recent financial year over which the trial data will be collected and will be reported in Euros. Unit costs will be retrieved mostly from Portuguese official sources.

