#### **6.17.5. Cost and cost-effectiveness analysis**

Costs will be modelled with the most appropriate distribution for data. All analyses will be adjusted for pre-specified baseline characteristics, plus baseline costs.

Cost-effectiveness will be explored in terms of the primary outcome measure (reduction in PPI use) and QALYs and, will be assessed through the calculation of incremental cost-effectiveness ratios (ICER) – the additional cost of one intervention compared with another divided by the additional effects – using the net benefit approach (107). Cost-effectiveness acceptability curves will be presented by plotting the probability of the intervention being cost-effective for a range of possible values of willingness to pay for unit improvements in outcome (108). These curves are a recommended decision-making approach to dealing with the uncertainty that exists around the estimates of expected costs and expected effects associated with the interventions under investigation.

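### Table 5 and section 6.17.2 set different recall periods for health-care use at the 6-month call, and they agree only when the call falls at exactly 6 months

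*Protocol*

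**What the plan says.** Four statements in the Protocol bear on the period that the T2 resource-use data cover.

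- **Table 5 (section 6.12)** heads the whole block of resource-use items "Healthcare resource utilization (within the last 6 months -T0 and T2". The look-back is the same fixed length at baseline and at T2.
- **Section 6.17.2** treats the two time points differently. For baseline: "At baseline, information will cover the previous 6 months". For T2: "at 6-month follow-up the service use since the previous time-point was recorded (baseline".
- **Section 6.8** sets the visit window: "Follow-up data can be collected within 1 month after or before these exact time-point". Section 6.12 repeats it for T1 and T2: "Follow-up data for T1 and T2 could be collected within 1 month after or before these exact time-points". T2 can therefore fall anywhere from 5 to 7 months after recruitment.
- **Section 6.17.1** fixes the period to be costed: "The time horizon in the base-case analysis will be of 6 months".

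The reported items feed directly into cost. For each item "a unit cost will be applied and the total costs for each individual will be calculated" (section 6.17.2). Section 6.15.2 also compares resource use between the arms as a secondary analysis.

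**The concern.** The two sections give the interviewer different questions for the same items. Outside the exact 6-month date, the answers refer to different stretches of time.

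The Table 5 wording is the more harmful of the two when the call is off-date, because the six-month look-back slides with the call. Called early, the patient reports use from before recruitment as if it were follow-up. Called late, the patient is never asked about the first weeks after recruitment. The wording in section 6.17.2 always starts at the right point, but its length varies while the horizon is fixed.

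This matters now, and not only at analysis, because the recall wording decides what is collected. For appointments, tests, emergency visits and admissions, Table 5 lists yes/no answers, counts, types, nights and expenses, but no event dates. Section 7 states that collection from clinical or hospital records is not feasible. Once the question has been asked over the wrong period, no statistical analysis plan can move events into or out of the window. What is at stake is patient-reported cost in the cost-effectiveness analysis, which is part of the trial's stated aim.

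**Working it through.** **Inputs**

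- Horizon: months 0 to 6, with recruitment at 0 (section 6.17.1).
- T2 call at *t* months, with *t* between 5 and 7 (sections 6.8 and 6.12).
- Table 5 rule: use from *t* − 6 to *t*.
- Section 6.17.2 rule: use from 0 to *t*.

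**Scheduled date first.** At *t* = 6 the Table 5 rule gives 6 − 6 = 0 to 6, and the section 6.17.2 rule gives 0 to 6. Both reproduce the stated 6-month horizon exactly.

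**Off the scheduled date**

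| T2 call | Table 5 covers | Inside 0–6 | Error under Table 5 | Section 6.17.2 covers | Length ÷ 6 |
|---|---|---|---|---|---|
| 5 | −1 to 5 | 5 months | 1 month before recruitment added; month 5–6 missing | 0 to 5 | 5/6 = 0.83 |
| 5.5 | −0.5 to 5.5 | 5.5 months | 0.5 month before recruitment added; last 0.5 missing | 0 to 5.5 | 5.5/6 = 0.92 |
| 6 | 0 to 6 | 6 months | none | 0 to 6 | 1.00 |
| 6.5 | 0.5 to 6.5 | 5.5 months | first 0.5 month lost; 0.5 beyond the horizon added | 0 to 6.5 | 6.5/6 = 1.08 |
| 7 | 1 to 7 | 5 months | first month lost; 1 month beyond the horizon added | 0 to 7 | 7/6 = 1.17 |

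**Difference between the two wordings.** At a constant rate of use, the Table 5 count divided by the section 6.17.2 count is 6/*t*: 6/5 = 1.20 at a 5-month call and 6/7 = 0.86 at a 7-month call.

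**Can it be repaired afterwards?**

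- *Use asked from baseline, late call:* months 0 to 6 are all inside the reported period, and the excess can be removed by using days observed.
- *Use asked from baseline, early call:* everything reported belongs to the horizon. Up to one month is unobserved and must be filled by assuming a rate.
- *Use asked over the last six months, either case:* the period has the right length but the wrong position. Without event dates, pre-recruitment events cannot be taken out and first-month events cannot be put back.

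**What sits in the first month.** In the intervention arm the GP contact is planned 1 to 2 weeks after recruitment (section 6.5), with pharmacist calls 2 and 4 weeks after the GP reports a decision. The month lost at a 7-month call is therefore an active one. The next field covers which parts of it have another source.

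**The case against.** The strongest reply is that Table 5 is only a list of variables and its heading can be read as shorthand for the scheduled interval. On that view section 6.17.2, which defines resource measurement, governs. The two agree on the scheduled date, and the Protocol gives no estimate of how many calls will be off-date. All of this is fair and limits the size of the problem. It does not remove the conflict: both statements are current text, and section 7 also discusses recall in terms of the last six months. The 6-month questionnaire (Annex 14) is a stand-alone document that is not shown, so the wording actually put to patients cannot be checked.

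A reader might also infer several stronger conclusions that the Protocol does not support.

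- *That six-month costs as a whole cover the wrong period.* Only patients called off the date are affected, each by at most one month at either end.
- *That the intervention's own GP contacts and medication changes are lost at late calls.* Intervention-related GP appointments are recorded on an ongoing paper form with number, date and type (Table 5), and section 6.17.3 costs them as intervention costs. PPI use is measured at baseline, 3 and 6 months, and medicines are also taken from the dispensing software. What has no second source is the other first-month use: non-intervention visits, tests, emergency use and admissions.
- *That one month is costed twice.* Section 6.17.5 says "All analyses will be adjusted for pre-specified baseline characteristics, plus baseline costs". Baseline cost is a covariate and is not added to follow-up cost. An early call under Table 5 does put a pre-recruitment month into the outcome, but that month is not summed twice.
- *That the arms will differ in cost because of call timing.* The research team makes the calls in both arms, and nothing in the Protocol says that timing will differ. As an illustration only, under the section 6.17.2 rule with no alignment and constant use, an assumed mean gap of 7 days would give 7/182.5 = 3.8%, and 14 days 14/182.5 = 7.7%. Neither gap has a source in the Protocol.
- *That having no scaling rule is itself an error.* Such rules are commonly left to the statistical analysis plan, which section 6.15 announces. The finding is the conflict in what is collected.

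**Conclusion.** The conflict is real and should be reconciled before any T2 call is made. It concerns the period asked about, and no later analysis can correct that from undated counts.

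Its size is moderate. Under the Table 5 wording an off-date patient has up to one month of follow-up replaced by time outside the horizon: pre-recruitment time at early calls, and time after month 6 at late calls. Under the section 6.17.2 wording the observed length is 83% to 117% of the horizon, which can be handled in the analysis. The economic evaluation and the between-arm comparison of resource use are affected. The primary outcome and the sample size are not.

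The interval arithmetic needs no assumption beyond the stated window. The ratios of 1.20 and 0.86 also assume a constant rate of use. Whether the error differs between arms is unknown.

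**What to change.** **Collection.** Adopt one rule in Table 5, section 6.17.2 and the 6-month questionnaire: all use from the recruitment date to the date of the T2 interview, with the recruitment date read out to the patient. Record the interview date for everyone. Table 5 as shown lists no T2 call date, and it lists the baseline interview date only in the intervention-arm block, so both dates should appear there for both arms.

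**Analysis.** Align patient-reported resource use to the 6-month horizon by days observed, for example by scaling or with a log-days offset. Leave one-off intervention costs unscaled; otherwise they would be multiplied by 6/5 = 1.20 at a 5-month call and by 6/7 = 0.86 at a 7-month call. Put QALYs on the same 6-month horizon, so that costs and effects refer to the same period. These lines may go in the statistical analysis plan.

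**Cost.** This takes a wording change in two places in the Protocol and one in the questionnaire, at most two date fields, and a few lines of analysis text. The small downside is that alignment assumes a roughly constant rate of use over the one-month window. That matters most at early calls, where up to one month is not observed at all.

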### **6.13. Data management and Quality control**

The filled patient-paper questionnaires, intervention paper forms and other data collection tools can be sent by mail or deliver in-person to the CRA that then will make the deliver to the research team. The database for the insertion of the questionnaires and other formularies data will be created specifically for the purpose of this study and tested to check for data integrity. Researchers will assure database quality processes are followed for completeness and accuracy, and in accordance with the following data validation plan: database will not allow the duplication of records. Electronic databases will be stored on a secure shared computer drive only accessible by study researchers and all paper forms collections will be kept in locked cabinets.

To ensure that no patient is enrolled twice in the study, variables regarding date of birth, gender and NHS number will be checked for duplicates. Only authorized personnel from within the research team will have access to patient or provider personal data. A unique patient study ID will be assigned, which will consist of the first letter of the person's first and last name, and their date of birth in the format DD/MM/YYYY. When this ID is not available, the NIF unique numerical identifier can be used as provided by patient.

Quality control procedures will be used to check data collection and storage. Data storage will be checked and compared with the information written on the paper questionnaires for a random sample of questionnaires, in accordance with the Acceptance Quality Level (AQL) (100). Patients' inclusion criteria will be double checked (pharmacy and research team). All errors will be corrected. Further checks for possible inconsistency in information will be performed and appropriate corrections will be made.

Study researchers are responsible to ensure that the study is conducted, and data are generated, documented, and reported in compliance with the protocol, accepted standards of Good Pharmacoepidemiology Practice, and all applicable legislation, rules and regulations relating to the conduct of the study.

All data protection procedures are further detailed in the Privacy Impact Assessment (PIA) of this study, complying with the requirements of the GDPR.

All instruments and questionnaires to be applied in the study are detailed in the supplemental material section of the protocol (annexes).

This research is conducted by CEFAR/infosaúde, the research center of the National Pharmacy Association (ANF), which has interests in this topic. The support by academic independent researchers, who do not receive any fees for collaboration, will guarantee that these interests do not interfere in the analysis and interpretations. These conflicts of interests will obviously be declared in all scientific publications.

#### **6.14. Data recording and document retention**

CEFAR must maintain source documents for each patient in the study, consisting of data collected at the pharmacy (including dispensing records), at the FHU by general practitioners and by telephone interview by the research team, containing demographic, PROs and clinical information.

#### **6.15. Statistical Methods**

A statistical analysis plan (SAP) will be drafted before any analysis takes place.

##### **6.15.1. General principles**

The null hypothesis proposes no difference in primary outcomes between intervention and control patients.

Descriptive statistics will be calculated for the full dataset and study arm. Categorical outcomes will be summarized by absolute and relative counts, including counts of missing observations. Continuous outcomes will be summarized by the number of non-missing values, mean, standard deviation (SD), median, lower and upper quartiles and minimum and maximum values.

The description of the baseline characteristics including the self-rated health status (SRH), the primary and secondary endpoints will be presented for all patients and stratified by arm and other subgroups (e.g., age group, etc.).

Comparisons between groups will be performed using the chi-square/Fisher test for categorical variables and/or t-test/ANOVA or nonparametric Wilcoxon/Kruskal-Wallis test for continuous variables. Significance level of 5% will be adopted.

### **6.15.2. Study outcomes**

An intention-to-treat population will be considered, including patients regardless to the degree to which they have been exposed to the intervention (as this is a pragmatic trial). Outcomes will be estimated for the whole dataset. 95% confidence intervals will be reported.

#### **Primary outcomes**

Primary outcome of the study will be calculated using a GLM model for binary outcome with an identity link function to estimate the risk difference or the difference between Intervention and Control groups in the proportion of patients who discontinued or decreased PPI dosage at 6 months of follow up. Results will be adjusted for baseline covariates. Relative risk will be computed as well as the number needed to treat (NNT) – the inverse of the difference in absolute rate of discontinuation between the intervention and control groups. Analysis will also be conducted at 3 months of follow up. A 1 year analysis can be conducted to measure the maintenance of the intervention effect. Significance level adopted is  $\alpha = 0.05$ .

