|             | 
considered, including patients regardless to the degree to which they have been exposed to the intervention (as this is a pragmatic trial). Outcomes will be estimated for the whole dataset. 95% confidence intervals will be reported.
 
The description of the baseline characteristics including the self-rated health status (SRH), the primary and secondary endpoints will be presented for all patients and stratified by arm and other subgroups (eg.: age group, etc.). Comparisons between arms will be performed using the chi-square/Fisher test for categorical variables and/or t-test/ANOVA or nonparametric Wilcoxon/Kruskal-Wallis test for continuous variables. Significance level of 5% will be adopted.
 
The primary outcome of the study will be calculated using a GLM model for binary outcome with an identity link function to estimate the risk difference or the difference between Intervention and Control groups in the proportion of patients who discontinued or decreased PPI dosage at 6 months of follow up. Results will be adjusted for baseline covariates. Relative risk will be calculated as well as the number needed to treat (NNT) – the inverse of the difference in absolute rate of discontinuation between the intervention and control groups. Analysis will also be conducted at 3 months of follow up. Significance level adopted is <math>\alpha = 0.05</math>.
 
Regarding secondary outcomes, descriptive statistics will be calculated for all patients and reported with respect to each time point. For each outcome, adequate GLM models will be used to compare groups with respect to therapeutic outcomes (PPI specific and other medication), Quality of life (EQ-5D-5L), BMQ specific applied to PPI, Adherence (MAT) and healthcare resource utilization. Changes over time points will be evaluated.
 
Patients' level of satisfaction and process outcomes will be analyzed only for the intervention arm. Process outcomes will be used to assess the fidelity and quality of the collaborative intervention.
 
Time to PPI discontinuation will be assessed through Kaplan-Meier (KM) estimator. Results will be stratified by group and KM curves will be presented. Log-rank test will be computed to compare results between cohort subgroups. In alternative, multivariate Cox Proportional Hazards models will be used if groups are unbalanced and hazard ratios computed.
 |

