#### Change in Patient Reported Outcomes Measures (PROMs):

- Quality of life related to health, will be evaluated using the five-level version of the European Quality of Life-5 Dimensions questionnaire (EQ-5D-5L instrument) (90,91), assessed at baseline and 6-month follow-up; EQ-5D-5L scores will be computed for each patient.
- Patients' beliefs about inappropriate medicines, assessed by the beliefs about medicines questionnaire (BMQ-specific)(92) applied to PPI; assessed at baseline and 3-month follow-up. It comprises two sub-scales: the specific necessity scale (SNS) assessing patients' views on their personal need for their medication and the specific concerns scale (SCS) assessing patients concerns towards their medication.
- Adherence using a self-reported 7-item Measure Treatment Adherence (MTA) tool (93), applied at baseline and 6-month follow-up. The MTA, a psychometric tool derived from Morisky et al, evaluates the individuals' behaviour in relation to the daily use of medication. Each item is scored from 1 (always) to 6 (never). Points are summed and divided by the total number of items. Higher scores indicate higher self-reported adherence. Patients with values of 5 and 6 are considered adherents. We select this method to measure multiple medication adherence because is simple to apply and was validated for the Portuguese Population in 2001, with a reported Cronbach's alpha of 0.74.

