#### **6.11. Sample size**

Our principal hypothesis is that our intervention will reduce the use of inappropriate PPIs compared to usual care.

Our assumption is that the intervention will reach a rate of discontinuation similar with that achieved in previous studies reporting medication withdrawals in intervention with collaborative work between pharmacists and GP, compared to usual care (minimum absolute difference of 20%)(79,97). Alongside,

we will also assume that a small rate of discontinuation will be observed in the group without the intervention (control Group) as much as of 10%.

Therefore, our study will be conducted to detect a minimal 20% increase in the rate of discontinuation of inappropriate medication use caused by the intervention compared with the usual care. Assuming an alpha of 5%, 90% power and an allocation ratio of 1:1, we estimate that the minimum total sample size to detect differences between intervention and control group is 178 patients (89 patients per group).

Considering a 20% lost to follow-up, then a total of 222 patients (111 per group) recruited in the participating pharmacies will be needed in this study.

The sample size was calculated using the software G\*Power version 3.1.9.6.

**Exact** - Proportions: Inequality, two independent groups (Fisher's exact test)

**Options:** Exact distribution

**Analysis:** A priori: Compute required sample size

|                |                             |   |           |
|----------------|-----------------------------|---|-----------|
| Input:  | Tail(s)                     | = | Two       |
|                | Proportion p1               | = | 0.1       |
|                | Proportion p2               | = | 0.3       |
|                | $\alpha$ err prob           | = | 0.05      |
|                | Power (1- $\beta$ err prob) | = | 0.90      |
|                | Allocation ratio N2/N1      | = | 1         |
| Output: | Sample size group 1         | = | 89        |
|                | Sample size group 2         | = | 89        |
|                | Total sample size           | = | 178       |
|                | Actual power                | = | 0.9017447 |
|                | Actual $\alpha$             | = | 0.0340267 |

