### Recruitment and selection bias

- The intervention FHUs were selected based on willingness to develop a collaborative intervention and may not represent a generalized sample of FHUs population.
- The pharmacies are also selected based on willingness to participate and may not represent a random sample from any well-defined population.
- Positive selection bias of patients: Strategies to minimize patient's self-selection will be adopted, namely a pop-up reminder at the pharmacy software whenever a PPI is dispensed during the recruitment period. We will also compare the characteristics between the patients who are approached and refused to participate in the study and the patients enrolled in the study.
- Some patients may be lost to follow-up during the study period. Depending on the volume of dropouts and missing data which may bias the data collection and the results, the baseline characteristics of this sub-group will be compared with the baseline characteristics of all patients recruited for the study per arm to assess any selection bias.
- To determine whether control allocation was effective descriptive statistics (means, proportions) will be calculated to assess the balance between the groups on important confounders such as age, sex, health status, baseline beliefs about medications and the burden of medicines. If such confounders are unbalanced between the groups, we will produce unadjusted and adjusted estimates of the primary and secondary outcomes.
- As General practitioner usual practices can also be a confounding domain, control patients were selected from the population served from FHUs in the control municipalities, with PPI prescription patterns similar to the interventions FHUs, defined by the volume of prescribed PPI per 1000 elderly ( $\geq 65$  y) in 2021, as FHU age pyramid.

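### The identity-link GLM fixed for the primary analysis will very probably not fit if it is adjusted for the confounders that the protocol itself names

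*Protocol*

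**What the plan says.** Protocol section 6.15.2 (Primary outcomes) fixes the estimator: the primary outcome is to be "calculated using a GLM model for binary outcome with an identity link function to estimate the risk difference" between arms at 6 months. It continues, without condition, "Results will be adjusted for baseline covariates", and asks for a relative risk and an NNT. The Statistical Methods row of section 1 repeats this. Neither place names the distribution family or lists the covariates.

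Section 7 (Recruitment and selection bias) names "important confounders such as age, sex, health status, baseline beliefs about medications and the burden of medicines" for a balance check and adds: "If such confounders are unbalanced between the groups, we will produce unadjusted and adjusted estimates of the primary and secondary outcomes". Section 6.8 describes the beliefs instrument (BMQ-specific) as having two sub-scales.

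Section 6.11 plans 89 evaluable patients per arm at 10% vs 30%. Section 6.15.4 restricts the primary analysis to patients with 6-month PPI data, so about 178 patients are analysed if losses are as planned. Section 6.15.2 promises 95% confidence intervals.

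**The concern.** A binomial model with identity link writes each patient's risk as a plain sum: intercept, plus arm effect, plus covariate contributions. Nothing in that form keeps the sum between 0 and 1. When the control risk is about 10%, the covariate contributions of any control patient may not add up to less than -0.10. As an illustration, one covariate with a slope of 0.05 per SD already takes a control patient 2 SD below the mean to 0.10 - 2 x 0.05 = 0. With several covariates and few events, the likelihood tends to peak on the edge of the permitted region. Software then stops with an error, fails to converge, or ends at a boundary where Wald intervals are not valid.

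The trial is not randomised. Section 6.1 matches areas and Family Health Units, but for the primary comparison the only stated control at patient level is this covariate adjustment. If the named model has no usable fit, the analyst must choose covariates or a method after seeing outcomes, or fall back on the crude difference.

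**Working it through.** **Inputs.** Rates 0.10 and 0.30, two-sided alpha 0.05, power 0.90 and 1:1 allocation (section 6.11). Six terms besides arm (sections 7 and 6.8): age, sex, health status, two BMQ scores, number of medicines.

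**The plan's own figure.** Exact power of the two-sided Fisher test by full enumeration is 0.8977 at 88 per arm and 0.9017447 at 89, so 89 per arm is reproduced. With 20% loss, 178 / 0.8 = 222.5, against 222 stated; the gap is rounding. The sample size is not in question.

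**Events available.** 89 x 0.10 = 8.9 in controls and 89 x 0.30 = 26.7 in the intervention arm, about 36 in all. Section 6.11 words the control rate as "small rate of discontinuation will be observed in the group without the intervention (control Group) as much as of 10"%, that is, an upper value. A lower rate would bring fitted risks closer to zero.

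**Simulation.** Trials of the planned size were generated and the model was fitted with the algorithm of R's glm (binomial, identity link, default starting values). A separate search checked whether any interior maximum exists: score near zero and all fitted risks strictly between 0 and 1. The documents give no covariate distributions or effects, so three settings were assumed: no effect, weak (log odds ratio 0.1-0.3 per SD) and moderate (0.2-0.6 per SD). There were 300 to 600 runs per setting, so the Monte Carlo standard error is at most sqrt(0.25/300) = 2.9 percentage points. Ranges run over the three settings.

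| Terms besides arm | Default fit converges | Interior maximum exists |
|---|---|---|
| None | 100% | 100% |
| Sex | 95-98% | 96% |
| Sex, age | 20-55% | 30-64% |
| Sex, age, number of medicines | 6-32% | 10-39% |
| All six | 0-6% | 0-7% |
| All six, dichotomised | 0.3-5% | 2-11% |
| All six, 111 per arm | 0-5% | 0-12% |
| All six, rates 20% vs 40% | 0-34% | 0-41% |

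Supplying feasible starting values did not help with all six terms (0-6%). Nor is misspecification the cause: in the no-effect setting the additive model is correct, and with six terms it still converged in only 5.2% of 600 runs.

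**Alternatives, six terms, 89 per arm, 600 runs per setting.**

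| Method | Fits | Mean RD (true 0.20) | 95% CI coverage | Power |
|---|---|---|---|---|
| Logistic regression, standardised, delta-method SE | 100% | 0.196-0.204 | 92.5-95.5% | 91-96% |
| Linear regression, robust SE | 100% | 0.196-0.204 | 94-97% | 90-95% |

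The Monte Carlo standard error of a 95% coverage at 600 runs is sqrt(0.95 x 0.05 / 600) = 0.9 points. The lowest delta-method figure, 92.5%, is therefore slightly below nominal, which is a reason to allow a bootstrap interval.

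**The case against.** The strongest reply is that the protocol does not fix the setup that fails.

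- **Covariates.** Section 6.15.2 gives no list. The list in section 7 is introduced as examples for a balance check, and adjusted estimates are tied there to imbalance. Failure depends on the number and coding of terms: with binary covariates only, a separate check under other assumed effects gave convergence of 98-99% with one, 58-79% with two, 33-58% with three and 0-11% with six. This stands. A reader might infer that sample size and event rate alone defeat the model; they do not.
- **Family.** Binomial is the natural reading for a binary outcome but is not stated. A Gaussian identity-link model with robust standard errors would satisfy the wording and always fits. This stands, and it is why saying so explicitly is one of the two remedies.
- **No estimate at all.** A boundary-constrained fit with a bootstrap interval would still give a risk difference. True, but that is not the plain GLM described.
- **Relative risk and NNT.** A reader might infer that an identity-link model cannot give an adjusted relative risk. It can: averaging fitted risks under each arm gives one. The protocol's NNT, the inverse of the absolute difference, is consistent with 1/RD.
- **Confounding.** A reader might infer that adjustment is the only protection. It is not: section 6.1 selects control municipalities on purchasing power, ageing and illiteracy, and control units by type and PPI prescribing within 20%.
- **SAP.** A covariate list and a fallback may be in the SAP, which is not at hand, so their absence from the protocol is no finding.

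What survives is narrower: the protocol does state an estimator and does state adjustment without condition, and a SAP that follows it inherits the difficulty.

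**Conclusion.** The concern holds in conditional form. Under the binomial reading, the stated model is safe unadjusted or with one binary covariate, unreliable with two covariates when one is continuous (about 20-55% convergence), and very unlikely to give a usable fit with the confounders that section 7 names (about 0-7%). The size rests on assumed covariate distributions and effects, on 89 evaluable patients per arm and on 10% vs 30%. With all six terms the fit failed in most trials under every assumption tried, including 111 per arm and 20% vs 40%. It is a should-fix: the estimand is sound and the sample size is unaffected, but the named estimator is a poor vehicle for the adjustment that this design needs.

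**What to change.** In section 6.15.2 (Primary outcomes) and the Statistical Methods row of section 1, replace the identity-link GLM with logistic regression on arm plus the baseline covariates, followed by marginal standardisation: predict each analysed patient's risk under both arms and average. Report the adjusted risk difference, relative risk and NNT (1/RD) from that one model, with delta-method or bootstrap confidence intervals.

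Alternatively, keep the identity link but state that the model is a linear (Gaussian) regression with robust standard errors.

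Either change costs one sentence in each place, with no new data and no extra patients, and should be made before outcomes are analysed.
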